### Accelerometer activity monitoring

The accelerometer (Aipermon^® ^GmbH, Germany) will be attached to the patient's belt and positioned above the left hip. Patients will wear the device during waking hours during intervention time. The accelerometer will be attached after dressing in the morning and only taken off for showering, bathing and sleeping. In the statistical analysis a day starts at 24.00 o'clock and ends at 23.59 o'clock the same day. Mean activity per day will be calculated. All device settings (date, time, weight, age and gender) are pre-programmed for each patient upon receiving it and the device is switched on throughout the entire measurement period to keep patient handling of the accelerometer to a minimum. Upon completion of the intervention, the data is copied onto a PC, and its contents are viewed via ActiCoach MPAT2Viewer, Aipermon^®^. Wearing-time include min/day spent passively (PAS: sitting), actively (ACT: movement, but not walking), walking (WLK: 0-5 km/h)) and fast walking (FWLK: > 5 km/h). These are computed and analyzed. Walking speeds from 0 to 80 m/min are detected as *Walking *and walking speeds from 83 to 115 m/min are detected as *Fast Walking*. Speeds above 115 m/min are considered *Sportive *at which point walking would turn into jogging in most individuals. Non-wearing time is indicated by the device as "resting mode". Walking and fast walking times are added to a total walking time (TWT). Activity modes and accelerometer detection accuracy have been extensively validated [46].

### Blinding

All testing procedures will be carried out by dedicated trained, blinded assessors. A further research assistant will be responsible for data input. The data will be analysed by the main author.

### Sample size and power calculation

In order to detect a clinically significant difference in the primary outcome measure of "Timed up and go" of 10 sec (from a likely range of 10-40 sec), with a probability of 80% at a two sided 5% significance level a total of 116 patients (58 per group) must enter the study. This calculation was performed assuming a SD of the timed up and go of 19 sec [52]. Since there are indications that the distributions of the primary endpoint variable is skewed, the use of a nonparametric test should increase the actual power. To allow for drop-outs 60 participants per intervention will be recruited.

### Randomization and allocation concealment

Subjects will be randomised into cane or TheraTogs group using a computer generated randomisation programme. Allocation will be concealed with group allocation contained in centrally held sealed envelopes at Maastricht University.

### Statistical methods

The primary analysis will be performed in an intention-to-treat fashion, i.e. all subjects who where randomised and have at least a Timed Up and Go assessment before start of therapy will be included in all analyses. In the primary analysis, missing values will be replaced by the last available value. If no value under or after treatment is available, the value measured before start of therapy will be used.

The primary analysis will be performed on the Timed Up and Go after 5 weeks of therapy. A nonparametric two sample Wilcoxon-Mann-Whitney test will be performed. Significance levels will be 5%. As robustness analyses, an analysis of covariance will be performed with the value before start of therapy as covariate and centre and therapy as factors. 95% CI's will be calculated based on this analysis. Descriptive statistics for all data will be presented. For continuous data, this will include the change from pre-therapy values. Pre-therapy values will be compared between groups to identify relevant co-variables.

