**Methods/Design:**

Multi-centre, single blind, randomised trial with 120 patients after first stroke. When subjects have reached Functional Ambulation Category 3 they will be randomly allocated into TheraTogs or cane group. TheraTogs will be applied to support hip extensor and abductor musculature according to a standardised procedure. Cane walking held at the level of the radial styloid of the sound wrist. Subjects will walk throughout the day with only the assigned walking aid. Standard therapy treatments and usual care will remain unchanged and documented. The intervention will continue for five weeks or until patients have reached Functional Ambulation category 5. Outcome measures will be assessed the day before begin of intervention, the day after completion, 3 months, 6 months and 2 years. Primary outcome: Timed "up and go" test, secondary outcomes: peak surface EMG of gluteus maximus and gluteus medius, activation patterns of hemiplegic leg musculature, temporo-spatial gait parameters, hemiplegic hip kinematics in the frontal and sagittal planes, dynamic balance, daily activity measured by accelerometry, Stroke Impact Scale. Significance levels will be 5% with 95% CI's. IntentionToTreat analyses will be performed. Descriptive statistics will be presented.

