### In- and exclusion criteria

All subjects (1) will be patients with hemiplegia following a first unilateral stroke, (2) will score at least level 3 on the Functional Ambulation Category (FAC) [39] (able to walk unaided on even ground but requiring verbal prompts and stand-by help without body contact) and (3) must have been independent walkers prior to insult without walking aids. (4) Subjects will have a Mini Mental State [40] score of 22 or above, (5) will have no orthopaedic or other neurological conditions that could limit walking ability, (6) have no gross visuospatial or visual field deficits and (7) will have no medical contraindications to walking.

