### Recruitment

Potential subjects will be identified by rehabilitation staff at the participating hospitals. Suitability for participation will be checked and confirmed by the researchers. Signed, informed consent will be obtained from subjects before inclusion and randomisation. Subjects will be randomised into TheraTogs (intervention) and cane (control) group (see below). Intervention will begin when patients have reached level 3 on the FAC.

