### Measures

Outcome measures will be taken at baseline, defined as the day before intervention begin, the day after intervention is completed (max. 5 weeks), 3 months, 6 months and 2 years after intervention begin.

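### The set called intention-to-treat drops randomised patients who have no pre-therapy Timed Up and Go, and nothing places that test before allocation is disclosed

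*Protocol article*

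**What the plan says.** **Analysis set.** Under Statistical methods, the primary analysis is described as intention-to-treat and then defined: "all subjects who where randomised and have at least a Timed Up and Go assessment before start of therapy will be included", and this applies to every analysis. Missing values are filled by carrying the latest one forward. For patients with nothing during or after treatment, "If no value under or after treatment is available, the value measured before start of therapy will be used". The only provision for a missing pre-therapy TUG is exclusion.

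**Primary test.** The same section specifies an unadjusted Wilcoxon-Mann-Whitney test on the TUG after 5 weeks. The pre-therapy TUG is a covariate in the robustness ANCOVA, which also supplies the 95% confidence intervals. It is used in change scores and in a comparison of the groups before therapy as well.

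**Timing of baseline.** Under Measures: "Outcome measures will be taken at baseline, defined as the day before intervention begin". Randomisation is not mentioned there. Randomization and allocation concealment says that sealed envelopes are kept centrally, but not when they are opened relative to baseline.

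**Timing of randomisation.** The Abstract (Methods/Design) says: "When subjects have reached Functional Ambulation Category 3 they will be randomly allocated into TheraTogs or cane group". In- and exclusion criteria makes FAC 3 or above a condition of entry. Recruitment says "Signed, informed consent will be obtained from subjects before inclusion and randomisation", describes the allocation, and closes with: "Intervention will begin when patients have reached level 3 on the FAC".

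**Blinding.** The Blinding section has trained, blinded assessors perform all tests.

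**The concern.** An intention-to-treat comparison is protected because membership of the analysis set is fixed at randomisation. Here membership also depends on something that may happen after randomisation, namely whether the patient completes a TUG before therapy. If the arm is already known by then, a patient who dislikes the assigned device can leave before the test and so leave the trial's analyses. A suit worn on the skin all day and a cane may not provoke this equally often, or in the same kind of patient.

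The rule also discards usable data. A patient whose baseline was missed but who was tested at 5 weeks has the outcome that the primary test needs, and is still removed.

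The same ordering bears on the baseline value itself. TUG time depends on effort, and a patient who knows the allocation may perform differently. That would affect the ANCOVA, and with it the only confidence intervals planned, the change scores, and any baseline carried forward as an outcome.

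**Working it through.** **1. What the rule does to each type of randomised patient**

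| Pre-therapy TUG | TUG at 5 weeks | Under the stated rule | Could the primary test use the patient? |
|---|---|---|---|
| yes | yes | included | yes |
| yes | no | included, value carried forward | yes, with the carried value |
| no | yes | excluded | yes, the outcome is observed |
| no | no | excluded | only with a further rule |

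The third row is an exclusion that the primary test does not require. In the fourth row, carrying forward cannot help unless some other TUG exists.

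**2. Order of events, section by section**

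- The Abstract and the entry criteria place FAC 3 at or before randomisation.
- Recruitment puts consent before randomisation and attaches FAC 3 to the start of the intervention. Read alone, it leaves room for a gap between randomisation and FAC 3. Read with the other two sections, it is an inconsistency.
- Measures fixes baseline relative to the intervention. Randomisation could fall on either side of it.
- No section says that the TUG precedes opening of the envelope.

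**3. The plan's own figure, and the effect on power**

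Inputs from Sample size and power calculation: difference 10 s, SD 19 s, 80% power, two-sided 5%, 58 per group, 60 per group recruited.

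Normal approximation: n = 2 × (1.960 + 0.842)² × (19/10)² = 2 × 7.849 × 3.61 = 56.67, so 57 per group. The two-sample t-test version gives 57.65, so 58 per group. The stated 58 is reproduced and is not in dispute.

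The document gives no rate of missing baseline TUG. For an assumed loss from 60 per arm:

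| Assumed loss | Left per arm | Power (normal) | Power (t) |
|---|---|---|---|
| 0% | 60 | 82.2% | 81.6% |
| 5% | 57 | 80.2% | 79.5% |
| 10% | 54 | 78.1% | 77.3% |
| 15% | 51 | 75.7% | 74.9% |

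Small losses cost little power. The issue is bias.

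**4. Illustration of bias (assumed inputs)**

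Suppose k of 60 patients are excluded from one arm and none from the other, and the excluded would have been d seconds slower than those retained, whose mean is m. The full-arm mean is [(60 − k)m + k(m + d)]/60 = m + kd/60, so exclusion shifts the arm mean by kd/60.

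- k = 3, d = 10: 30/60 = 0.50 s
- k = 5, d = 10: 50/60 = 0.83 s
- k = 9, d = 10: 90/60 = 1.50 s
- k = 9, d = 19 (a full SD): 171/60 = 2.85 s

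For scale, the standard error of the difference is 19 × √(2/60) = 3.47 s. The 0.83 s case is 8% of the 10 s target (0.83/10) and 0.24 standard errors (0.83/3.47). The last case needs a 15% loss confined to one arm, with excluded patients a whole SD slower on average. These are shifts in means, whereas the primary test is rank-based, so they indicate scale only.

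**The case against.** Several objections carry weight.

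- **Randomisation before FAC 3.** A reader might infer from Recruitment that patients are randomised before FAC 3 and that those who never reach it then disappear. The documents do not support that. The Abstract randomises at FAC 3, and the entry criteria make anyone below it ineligible. What remains is one sentence to reconcile.
- **The exclusion clause as proof of sequence.** A reader might take the clause to show that randomisation comes before baseline. It does not: a baseline scheduled before randomisation can still be missed or lost.
- **A baseline shaped by allocation.** This is possible only if the arm is disclosed first, which the text leaves open. Blinded assessors limit the risk, though they do not blind the patient's effort. Baseline reaches the primary test only through carrying forward.
- **A condensed article.** Day-level sequencing is commonly left to the full protocol, so silence on it would not be a finding by itself. That is fair. But the exclusion is stated text, and the open sequence is only the reason why it matters.
- **No real magnitude.** The example figures are assumptions, and most of them are small against the sampling error. This also stands.

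None of these answers the core point: the label and the definition differ, and the condition removes patients whom the primary test could use.

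**Conclusion.** The point holds in limited form. The set is a modified intention-to-treat set under an intention-to-treat label. It excludes some randomised patients needlessly, and the document does not rule out that exclusion depends on arm. The size of any bias cannot be estimated from the document and is probably small. The illustrations run from 0.50 s to 2.85 s, with the upper end resting on extreme assumptions. The conclusion assumes that some randomised patients lack a pre-therapy TUG, a case for which the clause itself provides. Dependence on arm further assumes that the arm can be known before baseline. Recruitment is inconsistent with the Abstract and the entry criteria on FAC 3, but this is a matter of reconciliation and does not permit randomising patients below the entry level.

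**What to change.** 1. **Sequence.** State in Recruitment, Measures, and Randomization and allocation concealment that consent is given, eligibility confirmed and the baseline TUG recorded before the envelope is opened.
2. **FAC 3.** Reconcile Recruitment with the Abstract and the entry criteria on the event to which FAC 3 is attached.
3. **Primary set.** Define it as all randomised patients, analysed in the arm assigned, and delete the condition on a pre-therapy TUG.
4. **Missing baseline in the ANCOVA.** Impute it; it should be rare once step 1 is in place.
5. **No TUG at any time.** Give an explicit rule, because imputing a baseline does not supply the outcome and carrying forward has nothing to carry. Multiple imputation or a worst-rank sensitivity analysis would serve, with the number of such patients reported by arm.

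If the present set is kept, call it modified intention-to-treat and report exclusions and their reasons by arm.

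The cost is mainly wording and the order of steps already planned, plus slight extra analysis work for items 4 and 5. No assessment is added.

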### Intervention details

Interventions will be applied for five weeks. If patients become independent walkers before this time (FAC 5) the intervention will be discontinued. If patients are discharged before this time and have not reached FAC 5 where possible the home carer will be instructed in the application of TheraTogs and the intervention will continue for 5 weeks as planned. TheraTogs will be applied as part of the washing/dressing routine in the morning by therapists or nursing staff instructed in the standard application. Subjects will walk throughout the day until preparing for bed with the prescribed walking aid. Standby assistance only will be provided during walking when necessary for safety. No other form of walking aid will be used for the duration of the study intervention. Foot or foot/ankle orthoses will remain unchanged and be worn as usual. All other forms of therapy (frequency and type) will remain unchanged and documented. Patients will receive usual care. When therapists feel that TheraTogs hinders treatment sessions the application may be removed for the duration of the session. It must be immediately reapplied with the standard application following treatment. When necessary TheraTogs may be removed for sleeping in the afternoon. It will be reapplied with the standard application on waking.

TheraTogs is worn directly on the skin. Attached to the basic suit hip abductor support [38] will consist of two broad straps attached 1.to the anterior torso, pulled downwards across the abductors towards and attached to the posterior aspect of the hemiplegic leg and, 2. to the posterior aspect of the torso pulled downwards to cross the abductors and attach to the anterior aspect of the hemiplegic leg. For hip extension one wide strap will be attached to the top of the pelvic rim on the non-hemiplegic side, pulled downwards and laterally passing across the buttock and towards the anterior aspect of the hemiplegic thigh attaching laterally (Figure 1.). Standard application training sessions will be provided to all staff before study begin. Written and photographic instructions will be provided. TheraTogs suits will be marked to ensure consistent application.

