## Discussion - implications of the hypothesis

Various forms of walking aids are commonly used in post stroke rehabilitation although the long term effects have been sparsely researched. In order to ensure the positive effect of these treatments and to enable evidence based practice, these interventions should be clinically researched.

Early walking is an important aim of stroke rehabilitation for many reasons including the psychological well-being of the patient, to prevent loss of cardiovascular fitness or the development of secondary musculoskeletal problems. This study questions whether canes are the optimal walking aid to enable early independent walking as their use inhibits rather than stimulates activity of the hemiplegic musculature and reduces the use of automatic balance responses contrary to the aims of rehabilitation. A possible alternative to cane use was recently tested by the authors in whom the immediate effects of TheraTogs were to significantly improve hip abductor muscle activity compared to cane walking or walking without walking aids [38].

The rate of recovery of all impairments after stroke is greatest in the first few weeks and slows down after two to three months. Kwakkel et al. discussed an early window during which rehabilitation has the most long term impact [17]. The potential negative or positive effects of walking aids may therefore be particularly significant in this early stage. To our knowledge no studies have investigated this question before. The results of this study may have important clinical significance and could be used in the development of guidelines for gait rehabilitation following stroke.

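### For a missed end-of-intervention visit, the primary analysis substitutes the pre-therapy Timed Up and Go, so it assumes no change in the weeks when recovery is expected to be fastest

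*Protocol article*

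**What the plan says.** The Statistical methods section of the protocol article fixes the primary time point, "The primary analysis will be performed on the Timed Up and Go after 5 weeks of therapy", and the handling of missing data. The rule has two steps. First: "In the primary analysis, missing values will be replaced by the last available value". Then a fallback: "If no value under or after treatment is available, the value measured before start of therapy will be used". The primary test is a Wilcoxon-Mann-Whitney test. The one robustness analysis described is an analysis of covariance with baseline, centre and therapy, and no different treatment of missing values is named for it.

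The Measures section places the assessments at baseline and then at "the day after intervention is completed (max. 5 weeks), 3 months, 6 months and 2 years after intervention begin". The Discussion says: "The rate of recovery of all impairments after stroke is greatest in the first few weeks and slows down after two to three months". The sample size section goes from 58 to 60 per arm: "To allow for drop-outs 60 participants per intervention will be recruited".

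**The concern.** The fallback speaks of values obtained during treatment, but no on-treatment TUG is scheduled. A patient lost between baseline and the end-of-intervention visit therefore has only the pre-therapy time to carry forward. The analysis then treats that time as an observed 5-week result.

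This errs in two directions. A patient who recovered as the Discussion expects is recorded as unchanged. A patient who deteriorated and can no longer do the test is recorded with the earlier time. At stake is the single confirmatory comparison: a true difference is diluted, and if the arms lose different proportions of patients, a difference appears that has nothing to do with the walking aid.

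The wording is also unsettled. A value obtained after treatment could be read to include the 3-month TUG, which would be a different rule.

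**Working it through.** **The plan's own figure.** Inputs from the sample size section: difference 10 s, SD 19 s, 80% power, two-sided 5%. The normal approximation gives 57 per arm (114 in total). The two-sample t-test gives 57.6, so 58 per arm and 116 in total, as stated. The drop-out allowance is 2 of 60 per arm, or 3.3%.

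**Expected difference under the rule.** Let R be the mean improvement in the cane arm, Δ the extra improvement with TheraTogs, and dT and dC the proportions missing the primary TUG in the TheraTogs and cane arms. Assume that loss is unrelated to the outcome and that the arms are balanced at baseline. A lost patient contributes zero change, so the expected difference is

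(R + Δ)(1 − dT) − R(1 − dC) = Δ − [(R + Δ)dT − R·dC].

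- With Δ = 0 this is −R(dT − dC), a bias against the arm with more loss.
- With equal loss d it is Δ(1 − d), which is dilution only.

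The article gives neither R in seconds nor loss by arm. R = 5, 10 and 15 s and the loss rates below, apart from the planned 3.3%, are assumptions.

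| Loss, TheraTogs v cane | R (s) | Bias against TheraTogs, no true effect (s) | Estimate, true effect 10 s |
|---|---|---|---|
| 3.3% v 3.3% (planned) | any | 0 | 10 × (1 − 2/60) = 9.67 |
| 10% v 10% | any | 0 | 10 × 0.90 = 9.0 |
| 15% v 5% | 5 | 0.5 | 10 − (2.25 − 0.25) = 8.0 |
| 15% v 5% | 10 | 1.0 | 10 − (3.00 − 0.50) = 7.5 |
| 15% v 5% | 15 | 1.5 | 10 − (3.75 − 0.75) = 7.0 |
| 20% v 5% | 5 | 0.75 | 10 − (3.00 − 0.25) = 7.25 |
| 20% v 5% | 10 | 1.5 | 10 − (4.00 − 0.50) = 6.5 |
| 20% v 5% | 15 | 2.25 | 10 − (5.00 − 0.75) = 5.75 |

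**Wilcoxon power by simulation.** 60 per arm, normal TUG with SD 19 s, baseline-to-outcome correlation 0.6 or 0.7 (assumed), loss at random, 4,000 trials per scenario. The fair comparator is the same test on observed values only, because lost patients cost power under any method.

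| Loss, TheraTogs v cane | Carried forward | Observed values only |
|---|---|---|
| none | about 79% | about 79% |
| 3.3% v 3.3% | about 77% | about 79% |
| 10% v 10% | about 68–71% | about 74–76% |
| 15% v 5%, R 5 to 15 s | about 49–62% | about 74–76% |
| 20% v 5%, R = 10 s | about 42% | about 74% |

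Repeat runs move these figures by up to two or three percentage points. At 20% v 5% with R = 10 s and no true effect, the type I error was about 6.6%.

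**The case against.** - **The planned loss is small.** At 3.3% per arm the estimate shrinks by a third of a second and the rule costs one or two points of power. This stands. The larger figures depend on assumed loss rates.
- **Part of any power loss is not due to the rule.** At 10% loss in both arms, roughly half of the fall from about 79% would occur on observed values anyway. This stands, and it is why the comparator is shown.
- **Unequal loss is not documented.** A reader might infer it from the Intervention details, where after discharge "where possible the home carer will be instructed in the application of TheraTogs". That sentence concerns continued use of the garment, not attendance for the TUG. Under intention to treat, a patient who stops wearing it can still be tested. Unequal loss therefore remains an assumption.
- **The null bias is modest.** The standard error is 19 × √(2/60) = 3.5 s, so 0.5 to 1.5 s is at most about 0.4 standard errors. If TheraTogs loses more patients, the bias also runs against the trial's hypothesis. Both are true, but the direction reverses if the cane arm loses more.
- **Large recovery is assumed.** R of 10 to 15 s plus a 10 s effect means 20 to 25 s of improvement with TheraTogs, most of the width of the stated likely range of 10 to 40 s. This is fair, and R = 5 s is therefore included.

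A reader might also infer that the rule always carries the pre-therapy value forward. The text does not go that far. Treatment can end early ("If patients become independent walkers before this time (FAC 5) the intervention will be discontinued"), and such a patient has a genuine post-treatment TUG the next day. The fallback wording might also admit a 3-month value. The point is limited to carrying forward from scheduled visits when the end-of-intervention TUG is missing.

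**Conclusion.** The concern holds in this limited form, as something that should be fixed. The rule is stated, not left open, and for a patient who misses the end-of-intervention TUG it supplies a value that the article's own account of recovery makes implausible. The harm is small if loss stays near 3.3% and equal. It becomes material if loss is clearly higher or unequal: about 7 to 8 s instead of 10 s at 15% v 5%, with power about 49–62% against 74–76% on observed values. Those figures rest on assumed recovery, assumed loss rates, an assumed correlation, normal data and loss unrelated to outcome. A reader might conclude that the primary result is certain to be invalid; the documents do not support that, because they give no evidence of heavy or unequal loss of TUG data.

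**What to change.** In Statistical methods, replace carrying forward in the primary analysis with multiple imputation within arm, using baseline TUG, centre, time since stroke and any 3- or 6-month TUG. A Wilcoxon statistic has no model estimate to pool, so the text must say how results are combined. Either analyse the imputed data with the baseline- and centre-adjusted analysis of covariance pooled by Rubin's rules, on a log or rank scale if TUG is skewed, or state a combining rule for the Wilcoxon statistic.

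Keep the carried-forward analysis as a sensitivity analysis, and say there whether a 3-month value may fill a missing 5-week value. Add a Wilcoxon sensitivity analysis that gives the worst rank to patients who died or cannot complete the test.

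The cost is revised wording and a little more programming, with no new data. The downside is reliance on a missing-at-random assumption. The change should be made before outcome data are seen.

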## Abstract

**Background:**

Annually, some 9000 people in Switzerland suffer a first time stroke. Of these 60% are left with moderate to severe walking disability. Evidence shows that rehabilitation techniques which emphasise activity of the hemiplegic side increase ipsilesional cortical plasticity and improve functional outcomes. Canes are commonly used in gait rehabilitation although they significantly reduce hemiplegic muscle activity. We have shown that an orthosis "TheraTogs" (a corset with elasticated strapping) significantly increases hemiplegic muscle activity during gait. The aim of the present study is to investigate the long term effects on the recovery of gait, balance and social participation of gait rehabilitation with TheraTogs compared to gait rehabilitation with a cane following first time acute stroke.

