The authors suggest that balance rehabilitation should attempt to restore balance strategies used by healthy individuals--namely fixed support responses requiring fewer cognitive resources in unchallenging situations. However cane use increases the base of support when walking through use of the arms. This strategy may emphasise use of cortical networks used for reaching "change of support" reactions. It emphasises use of cognitive resources on safe level ground and reduces the use of "fixed support" strategies. The authors suggest this leads to a long term reduction of automatic balance responses. It may be that because cognitive resources are needed in safe, level environments fewer additional resources are available for more difficult conditions such as walking outside or on public transport. The long term effects of canes on balance recovery and functional gait following stroke has to our knowledge been investigated in one study [37]. Balance recovery and community participation were shown to be reduced.

Taking all of these considerations together, the authors suggest that an optimal walking aid for post stroke gait rehabilitation would provide enough support to enable independent early walking without reducing hemiplegic muscle activity or inhibiting the use of balance reactions. The immediate effect of an elasticised orthotic walking aid (TheraTogs) on hemiplegic hip abductor activity has been previously investigated by the authors [38]. Activity in gluteus medius was increased by 16.5% compared to walking without aids when walking with TheraTogs (with cane use activity in gluteus medius was reduced by 22% compared to walking without aids). The increased activity with TheraTogs may be due to increased proprioceptive input provided by the orthosis or to the physical shortening of the muscle leading to increased overlap between the actin and myosin filaments and consequently a stronger contraction.

The authors hypothesize that cane use will inhibit activity on the hemiplegic side leading to reduced ipsilesional cortical activity and poorer long term functional gait outcomes. In contrast we hypothesize that TheraTogs will increase activity on the hemiplegic side during walking leading to increased ipsilesional cortical activity and improved long term functional gait outcomes.

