We further hypothesize that cane use will inhibit the use of normal balance reactions leading to reduced balance recovery and poorer social participation. As no external support is provided with the TheraTogs orthosis the use of automatic balance responses will not be inhibited during walking. This will result in improved balance recovery and social participation.

The aim of this study is to investigate the long term effects of canes and TheraTogs on the recovery of motor control and co-ordination, gait, daily activity, balance and social participation when used in early gait rehabilitation following stroke.

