### Primary outcome

The primary outcome measure will be the time taken to complete the Timed "Up and Go" Test [41]. This is a basic test for functional mobility which has good reliability and validity [41,42]. The seat height will be 65% of the subjects leg length and subjects will turn towards the unaffected side [43].

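### The aim and gait hypotheses are long-term, but the one stated between-arm outcome test is on Timed Up and Go at 5 weeks, when treatment ends

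*Protocol article*

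**What the plan says.** The abstract (Background) gives the purpose as follows: "The aim of the present study is to investigate the long term effects on the recovery of gait, balance and social participation". The last paragraph of the Background in the main text repeats it: "The aim of this study is to investigate the long term effects of canes and TheraTogs on the recovery of motor control and co-ordination". The two gait hypotheses in the same section carry the same horizon. For canes, the chain of events is expected to end in harm: "leading to reduced ipsilesional cortical activity and poorer long term functional gait outcomes". For TheraTogs it is expected to end in benefit: "leading to increased ipsilesional cortical activity and improved long term functional gait outcomes".

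The Measures section schedules assessments at baseline, the day after the intervention is completed (5 weeks at most), and then "3 months, 6 months and 2 years after intervention begin". The Primary outcome section names TUG time as the primary outcome and gives no visit. The visit is fixed only under Statistical methods: "The primary analysis will be performed on the Timed Up and Go after 5 weeks of therapy". The test there is a Wilcoxon-Mann-Whitney test at 5%. An analysis of covariance with baseline TUG, centre and therapy serves as the robustness analysis and supplies the 95% confidence intervals. Descriptive statistics are promised for all data. For the primary analysis, a missing value is replaced by the last one available.

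**The concern.** The question posed and the test that decides the trial sit at different times. The hypotheses concern where patients end up after early rehabilitation with one aid or the other. The decisive comparison is made as the intervention finishes, and it says nothing about whether a difference found then is still present at 6 months or 2 years.

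What is at stake is the conclusion. The Discussion justifies the trial by the lack of research on long-term effects of walking aids, and the article hopes the results will feed clinical guidelines. If the 5-week test is positive, there will be pressure to report it as an answer to the long-term aim. If it is negative, a late difference that matches the hypothesis will have no agreed standing. In either case the basis for a durability claim should be settled before the data are seen.

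**Working it through.** **1. The aim set beside the test.**

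| Element | Section | Time frame |
|---|---|---|
| Aim | Abstract; end of Background | Long-term |
| Gait hypotheses, both arms | Background | Long-term |
| Primary outcome (TUG) | Primary outcome | None given |
| Visits | Measures | End of intervention, 3 months, 6 months, 2 years |
| Primary between-arm test | Statistical methods | 5 weeks |
| Robustness analysis of covariance | Statistical methods | Supports the same comparison |

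The comparisons in the Analysis section are with baseline, with normal values or with the unaffected leg, not between arms. The other between-group comparison under Statistical methods is of pre-therapy values. So the only between-arm outcome test the article states is the one at 5 weeks.

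**2. The plan's own sample size.** Inputs from Sample size and power calculation: difference 10 sec, SD 19 sec, two-sided 5%, power 80%.

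n per arm = 2 × (1.960 + 0.842)² × (19/10)² = 2 × 7.85 × 3.61 = 56.7, so 57 by the normal approximation. The t-test version gives 57.6, so 58 per arm and 116 in total, exactly as stated. There is no arithmetic error.

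**3. The loss the plan allows for.** 60 per arm are recruited against 58 needed: 1 − 58/60 = 3.3%.

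**4. What the same 120 patients give at a late visit.** The article gives no late-visit effect, SD or loss rate. I keep 10 sec and 19 sec and assume 10% to 30% loss. Evaluable per arm: m = 60 × (1 − loss). Power = Φ(10 / (19 × √(2/m)) − 1.960).

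| Assumed loss | m per arm | Power | Randomised per arm to keep 58 (58 / (1 − loss), rounded up) |
|---|---|---|---|
| 10% | 54 | Φ(0.775) = 78.1% | 65 (130 in total) |
| 20% | 48 | Φ(0.618) = 73.2% | 73 (146 in total) |
| 30% | 42 | Φ(0.452) = 67.4% | 83 (166 in total) |

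So a late comparison is feasible as a secondary endpoint with the planned numbers, at less than 80% power. Making it the primary would call for a larger trial. These figures are for an unadjusted comparison of means. Adjustment for baseline TUG could recover some power, but the article gives no correlation from which to say how much.

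**The case against.** The best defence is that an end-of-treatment primary with longer follow-up is a common and reasonable design, and that the article gives a rationale for it. The Background says that recovery in the first weeks largely determines long-term function, and the Discussion speaks of an early window in which rehabilitation has most lasting impact. This supports measuring early and is a good reason to leave the primary where it is. It does not show that a difference between arms at 5 weeks will persist. That early status predicts later status across patients is a prognostic statement. Persistence of a treatment difference is what the trial sets out to learn.

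Three stronger readings are tempting, and the documents do not support them.

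- A reader might infer that the later visits have no planned analysis. The article is a condensed account, and a statistical analysis plan that is not shown may supply tests or models for them. Their absence here is not the point. The point is the mismatch between the stated aim and the visit that the article itself fixes.
- A reader might infer an inflated false-positive rate from choosing the best of several later visits. No section describes or invites such a choice, the article promises descriptive summaries for these data, and the 5-week visit is prespecified, so error control on the primary is intact.
- A reader might infer that the 5-week test can only pick up the device acting while worn. The assessment is on the day after the intervention is completed, and the Testing procedure does not say whether an aid is used during TUG, so this cannot be judged.

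It is also fair to object that gating a late test on the 5-week result blocks a formal claim for a benefit that emerges only later. That stands, and is a cost of the fix.

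**Conclusion.** The concern holds as a mismatch within the article. The question is long-term and the one stated between-arm outcome test is at the end of treatment, so a positive primary result would establish an end-of-treatment difference and no more. The 5-week test itself is not wrong, and the sample size reproduces. What is affected is what the trial may conclude. It is worth correcting before analysis but is not a fatal flaw, because the late TUG data are already scheduled. The power range of about 78% to 67% rests on an assumed 10% to 30% loss and on the planned difference and SD still applying at the late visit. The article gives no figure for any of these at that time.

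**What to change.** Keep TUG at 5 weeks as the primary analysis. Then:

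1. Name one late TUG visit from the existing schedule as the key secondary between-arm comparison. Six months is an example; which visit best represents a long-term effect is for the sponsor to decide and justify.
2. Test it at two-sided 5% only if the primary test is significant. This fixed order needs no split of alpha.
3. Adjust for baseline TUG and centre, and do not fill a missing late value with the 5-week one. Carrying it forward would build in the persistence that the comparison is meant to examine.
4. State that a long-term benefit will be claimed only on that test. If the sponsor does not want such a test, reword the aim and the conclusions to the effect at the end of treatment.

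The cost is a short addition to the analysis plan, with no new visits and no change to the primary or its alpha. There are two downsides. No formal long-term claim is possible if the 5-week test fails, even if a difference appears later. Power at the late visit will probably be below 80%, so a non-significant late result should be reported with its confidence interval and not read as evidence that the effect has gone.
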